## Abstract

**Background:**

Stroke is the third-leading cause of death and the leading cause of long-term neurological disability in the world. Cognitive, communication, and physical weakness combined with environmental changes frequently cause changes in the roles, routines, and daily occupations of stroke sufferers. Educational intervention combines didactic and interactive intervention, which combines the best choices for teaching new behaviors since it involves the active participation of the patient in learning. Nowadays, there are many types of interventions or means to increase adherence to treatment.

**Objective:**

The aim of this study is to enable patients who have suffered stroke and been discharged to their homes to improve the performance of the activities of daily living (ADL) in their home environment, based on advice given by the therapist. A secondary aim is that these patients continue the treatment through a reminder app installed on their mobile phones.

**Methods:**

This study is a clinical randomized controlled trial. The total sample will consist of 80 adults who have suffered a stroke with moderate severity and who have been discharged to their homes in the 3 months prior to recruitment to the study. The following tests and scales will be used to measure the outcome variables: Barthel Index, the Functional Independence Measure, the Mini-Mental State Examination, the Canadian Neurological Scale, the Stroke Impact Scale-16, the Trunk Control Test, the Modified Rankin Scale, the Multidimensional Scale of Perceived Social Support, the Quality of Life Scale for Stroke, the Functional Reach Test, the Romberg Test, the Time Up and Go test, the Timed-Stands Test, a portable dynamometer, and a sociodemographic questionnaire. Descriptive analyses will include mean, standard deviation, and 95% confidence intervals of the values for each variable. The Kolmogov-Smirnov (KS) test and a 2x2 mixed-model analysis of variance (ANOVA) will be used. Intergroup effect sizes will be calculated (Cohen’s d).

**Results:**

Currently, the study is in the recruitment phase and implementation of the intervention has begun. The authors anticipate that during 2015 the following processes should be completed: recruitment, intervention, and data collection. It is expected that the analysis of all data and the first results should be available in early-to-mid 2016.

**Conclusions:**

An educational intervention based on therapeutic home advice and a reminder app has been developed by the authors with the intention that patients who have suffered stroke perform the ADL more easily and use their affected limbs more actively in the ADL. The use of reminders via mobile phone is proposed as an innovative tool to increase treatment adherence in this population.

**Trial Registration:**

ClinicalTrials.gov NCT01980641; https://clinicaltrials.gov/ct2/show/NCT01980641 (Archived by WebCite at http://www.webcitation.org/6WRWFmY6U).

## Introduction

Stroke is the third leading cause of death and the leading cause of long-term neurological disability in the world [1-3]. In Europe, 250 people per 100,000 suffer strokes each year, and this trend is worsening with time [1,4]. More than half of all patients who survive a stroke suffer a severe disability that causes limitations in their independent functioning and their performance of activities of daily living (ADL) [1,3-5]. The prevalence of stroke is around 2% in people over 20 years of age, increasing to 6 to 7% for those over 65. In men, 66.5% of strokes occur in people over 65 years old, while in women this percentage increases to 80.3% [6,7].

Researchers have examined the impact of stroke on patients who have suffered one and they have shown that cognitive, communication, and physical weakness combined with environmental changes frequently cause changes in roles, routines, and daily occupations [8-11].

Stroke patients often receive treatment from a multidisciplinary team, such as physiotherapy or occupational therapy, during their stay in hospital or in a rehabilitation service after home discharge [5,12-14]. There are even some cases in which stroke survivors receive aerobic and endurance training [15], strength, balance, and coordination training [16], a comprehensive geriatric intervention [17,18], or functional activity training [19] at home.

Another type of treatment is educational intervention, which is used in patients with different pathologies and even with professionals, thanks to its proven effectiveness [20-23]. Educational intervention combines didactic and interactive intervention [24], which combines the best choices for teaching new behaviors since it involves the active participation of the patient in learning [23]. The effectiveness of this intervention lies in the fact that patients synthesize and apply what they have learned, which is a reinforcement learning behavior [20,21]. In turn, the educational intervention can offer cost savings in the rehabilitation process because of the possible reduction in patient visits to their general practitioner, the emergency department, and/or specialists, as well as reduction in the use of drugs [25].

Some studies have shown the application of this type of intervention in people who have suffered a stroke as a means to reduce the risk of secondary stroke [26]. Educational intervention in this population remains unusual, however, despite being in great demand, due to the lack of information individuals often encounter in their rehabilitation process [26,27]. Therefore, in order to allow for continuity and applicability to the previous rehabilitation treatment received in the hospital, we propose an educational intervention at home for people who have suffered a stroke and who have been discharged to their homes in the 3 months prior to recruitment to the study. The therapist—using a tool for home therapeutic counselling—will perform an ergonomic assessment of the home and of the execution of the ADL by the participant. Subsequently, based on the items not presented ​​in the tool, he or she will provide advice on the correct or easiest way to perform ADL, on which adaptations they should make at home, and on what kind of technical assistance could be useful for them [28,29].

Patient satisfaction regarding information and knowledge about treatment are key to adherence to this therapy by patients with long-term diseases [30]. Nowadays, there are many types of interventions used to increase adherence to treatment, such as Web-based programs, video conferencing, or other means that are available due to technological advances [31,32].

Furthermore, mobile phones are increasingly being used in clinical practice to assess patients or for more precise tracking [32-35]. The development of mobile phone apps has favored diagnosis and early intervention in people who have suffered, or will suffer, a stroke [33-35]. Memory-aiding therapeutic apps have helped to improve the results of interventions for stroke patients as a result of the inclusion of the patients as an active part of the treatment [32].

Therefore, in this study we propose the development of a mobile phone app that acts as a daily reminder of the advice that was given to patients by the therapist during the educational intervention in their homes.

The aim of this study is that patients who have suffered stroke and have been discharged to their homes improve the performance of ADL in their home environments, following the restrictions caused by the stroke, after having been given advice by the therapist. A secondary aim is that these patients continue the treatment through a reminder app installed on their mobile phones (mHealth).

The hypothesis of this study is that patients who have suffered stroke will perform the ADL more easily and use their affected limbs more actively in the ADL after an educational intervention. The use of reminders via mobile phone is proposed as a tool to increase treatment adherence.

## Methods

### Design

This study is a clinical randomized controlled trial (RCT) and will be conducted following the CONSORT rules for reporting [36]. This trial has been registered with ClinicalTrials.gov (NCT01980641).

### Participants

The total sample will consist of 80 adults who have suffered a stroke with moderate severity (score between 0 and 49 on the Barthel Index [37]), who have been discharged to their homes in the 3 months prior to recruitment to the study [28]. The sample will be taken from the Carlos Haya Hospital complex in Málaga, Spain.

Individuals with dementia or other severe cognitive impairment (scoring 0 to 17 in the Mini-Mental State Examination) will not be included [38].

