### Randomization

In stage 1, the sample will be divided into two groups of 40 participants each—experimental group and control group. The allocation and the randomization will be performed by a blinded researcher. The assignment of subjects to each group will be made through a system of sealed envelopes. Subsequently, for the pilot study in stage 2, we will create a group that will receive the app reminders on their mobile phones—the mobile phone group—and another group that will not receive the app reminder—the no mobile phone group. Group allocation will depend on whether the participant has a mobile phone and if its characteristics are adapted to the requirements of the study.

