### Statistical Analyses

Descriptive analyses will include mean, standard deviation, and 95% confidence intervals of the values for each variable. The normality of the variables will be performed using the Kolmogov-Smirnov (KS) test. Preintervention values prior to each condition will be compared. A 2x2 mixed-model analysis of variance (ANOVA) with supplementation (mobile phone group or no mobile phone group) as the between-subjects variable, and time (pre- and postintervention) as the within-subjects variable will be used. Intergroup effect sizes will be calculated (Cohen’s d). An effect size <0.2 reflects a negligible difference, between ≥0.5 and ≤0.8 a moderate difference, and ≥0.8 a large difference. A *P* value <.05 will be considered statistically significant. Data will be analyzed using SPSS version 19.0.

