## Discussion

### Implications of the Study

The aim of this study is that patients who suffer stroke and who have been discharged to their homes improve the performance of ADL in the home environment, in spite of the restrictions caused by the stroke, after advice given by the therapist. A secondary aim is that these patients continue the treatment through a reminder app installed on their mobile phones (isoTimer).

Some studies have analyzed the ergonomics of the workplace through a tool and other studies have carried out different kinds of treatments at home on people with stroke. Because of this, it is thought that an educational intervention at home with people who have suffered a stroke and who have been discharged to their homes could be an innovative and necessary study.

The use of a mobile phone reminder app is an innovative method because the mobile phone has been used with people who have suffered a stroke, but it has not been used before as a means of improving adherence to treatment at home with this population. This method could result in advances in facilitating the continuity of treatment in this population once they return to their homes.

This study could be a breakthrough in the treatment of people who have suffered a stroke and who have been discharged to their homes, since during the first months the largest changes occur and it is essential to continue the rehabilitation treatment received at the hospital. The HTAS tool would allow a proper assessment of the home environment and the implementation of the ADL by the patient, bringing some useful advice that will guide them through the process of recovery of functional independence. Also, being able to have an app that reminds them of the advice provided by the therapist ensures that all patients who suffer a stroke and are discharged to their homes do not encounter barriers in the environment, and that they can advance their functional independence. Additionally, this continuity in the treatment without interruption and its early implementation would favor not only the recovery and rehabilitation of the patient, but could also result in cost savings in care services.

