### Conclusions

The aim of this project was that patients who have suffered a stroke and been discharged to their homes can continue with the rehabilitation treatment received at the hospital. This treatment should occur without interruption and in the shortest time possible in order for patients to achieve the highest possible level of functional independence, and so that their readaptation to the environment is optimal. To do this, there will be a therapist intervention using the HTAS tool and an app (isoTimer) that will communicate reminders of the advice. The potential effectiveness of this educational intervention lies in the active participation of the patient.

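### Participants enter at any point in the 3 months after discharge, but the only analysis model described does not use time since discharge: an avoidable loss of precision in stage 1, not a bias

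*Protocol article*

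**What the plan says.** **Entry.** The Participants section takes adults "who have been discharged to their homes in the 3 months prior to recruitment to the study". It sets no lower limit and no bands within the window.

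**Recovery.** Implications of the Study explains why the intervention is timely: "since during the first months the largest changes occur and it is essential to continue the rehabilitation treatment received at the hospital". It goes on to expect that early implementation without a break would favour recovery and could save costs. The Conclusions add: "This treatment should occur without interruption and in the shortest time possible".

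**Formal aim.** The Introduction wants patients to "improve the performance of ADL in their home environments, following the restrictions caused by the stroke, after having been given advice by the therapist". Neither this aim nor the hypothesis mentions how soon after discharge the advice is given.

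**Allocation.** For stage 1, "the sample will be divided into two groups of 40 participants each". As to method, "The assignment of subjects to each group will be made through a system of sealed envelopes". No stratification factor is named. The stage 2 groups are not randomised: "Group allocation will depend on whether the participant has a mobile phone and if its characteristics are adapted to the requirements of the study".

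**Analysis.** Statistical Analyses gives one model, a 2x2 mixed ANOVA. Its between-subjects factor is mobile phone versus no mobile phone, and "time (pre- and postintervention) as the within-subjects variable will be used". No covariate is named. The Procedure section puts the stage 1 assessments at 2 and 4 weeks after the initial one and says the experimental and control groups will be compared, but gives no model for that comparison.

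**The concern.** By the document's own account, recovery is fastest early on. Someone who enters just after discharge and someone who enters near 3 months may therefore expect different spontaneous gains over the same 4 weeks. A pre/post comparison removes stable differences in level between participants. It does not remove differences in rate of change, which are what a wide entry window brings in. The time factor in the ANOVA is before versus after the intervention, so it does not capture this.

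Two things are at stake. The first is precision, in a trial of 40 per arm whose power is modest at its own planning effect size. The second is the wording of the Discussion and Conclusions. They link benefit to an early, unbroken start, while the design gives no comparison of earlier with later start and admits participants up to 3 months after discharge.

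**Working it through.** **Inputs from the article.** 40 per group, d = 0.59, alpha = .05 (sidedness not stated) and beta = .08 as printed, all from Sample Size Calculation; entry window 0 to 3 months, from Participants.

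**Assumed, because the article gives no figure.** R², the share of the variance behind d that time since discharge explains: 0.05 to 0.20. Entry spread uniformly over 0-90 days.

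**1. The plan's own figure.** n per group = 2(z_alpha + z_beta)²/d².
- Two-sided, 80% power: 2(1.960 + 0.842)²/0.59² = 45.1, so 46.
- Two-sided, 92% power (beta = .08 as printed): 66.
- One-sided, 80% power: 36.
- One-sided, 92% power: 54.

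None of these gives 40. That is a separate matter, but it fixes the starting point here. Two-sided power at 40 per group is Φ(0.59/√(2/40) − 1.96) = Φ(2.639 − 1.96) = 75.1% (74.1% with the noncentral t).

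**2. Effect of adjustment.** A covariate with share R² scales the SD by √(1 − R²), so power = Φ(2.639/√(1 − R²) − 1.96).

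| R² (assumed) | Two-sided power at 40 per group | n per group for 80% power |
|---|---|---|
| 0 | 75.1% | 46 |
| 0.05 | 77.3% | 43 |
| 0.10 | 79.4% | 41 |
| 0.20 | 83.9% | 37 |

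**3. Chance imbalance in stage 1.** SD of entry time = 90/√12 = 26.0 days. SE of the between-arm difference in means = 26.0 × √(2/40) = 5.8 days. The 95% range is ±1.96 × 5.8 = about ±11.4 days. An imbalance at that limit moves the contrast by 1.96√R² of its unadjusted standard error: 1.96√0.05 = 0.44 and 1.96√0.20 = 0.88. The standard error already allows for this; it is not an additional error.

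**4. Could an early-versus-late contrast be informative?** Split at the middle of the window, there are 20 per cell. The interaction has SE √(4/20) = 0.447 SD, and 80% power needs (1.96 + 0.842) × 0.447 = about 1.25 SD. That is roughly twice the planned main effect (1.25/0.59 = 2.1).

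**The case against.** The strongest reply is that stage 1 has a concurrent randomised control assessed at the same times. Natural recovery acts on both arms alike, and chance imbalance is already within the standard error and the 5% error rate. This stands. A reader might infer from the wide window that natural recovery biases the stage 1 effect; the design described does not support that. The argument does not extend to stage 2, where groups follow phone ownership, but that is a different question.

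Second, the ANOVA is written for the phone groups, and covariates are commonly left to an analysis plan that is not shown. This also stands in part. The article does not show that the stage 1 analysis omits time since discharge, only that the one model it describes does not use it.

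Third, a reader might infer that an early-continuity hypothesis goes untested. The formal aims and hypothesis contain no timing element, and the Discussion is worded conditionally, so no stated hypothesis is left without a test. Nor do months since discharge equal months without rehabilitation: the Introduction notes that patients may attend a rehabilitation service after going home.

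Fourth, the Discussion does not say whether the first months count from stroke or from discharge. Days since discharge may therefore be an imperfect marker of recovery phase, and the gain could lie at or below the low end of the range.

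What survives is that the document itself expects change to depend on phase, the variable comes from a date already collected, and using it is nearly free. The timing statements still go further than the design can show.

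**Conclusion.** The point holds in a limited form. Entry across the 3 months after discharge overlaps the period the article describes as that of the largest changes, and the only model it describes ignores time since discharge. In randomised stage 1 the consequence is lost precision, not bias. The article gives no recovery rate and no correlation, so the loss cannot be derived from it. For an assumed R² of 0.05 to 0.20, adjustment would move two-sided power from about 75% to 77-84% at 40 per group and d = 0.59.

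A reader might also conclude that allocation must be stratified by time since discharge. That does not follow, because the covariate alone recovers the precision at issue. The statements on early and uninterrupted implementation need limiting because no comparison in the trial bears on them, not because a formal aim has failed.

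**What to change.** 1. Prespecify days since discharge at recruitment as a baseline covariate in the stage 1 experimental-versus-control analysis, and state that model explicitly. The discharge date is already needed to apply the eligibility rule. The cost is one of about 78 error degrees of freedom (80 − 2).
2. Treat stratified envelopes as optional. The article reports that recruitment has begun, so new strata would change the allocation procedure part-way through.
3. Do not rely on a group by days-since-discharge interaction. At about 1.25 SD for 80% power it would be close to uninformative; if reported, label it exploratory.
4. In Implications of the Study and in the Conclusions, limit the statements to advice given within 3 months of discharge, and do not attribute benefit to early or uninterrupted implementation. This costs only wording.

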### Randomization

In stage 1, the sample will be divided into two groups of 40 participants each—experimental group and control group. The allocation and the randomization will be performed by a blinded researcher. The assignment of subjects to each group will be made through a system of sealed envelopes. Subsequently, for the pilot study in stage 2, we will create a group that will receive the app reminders on their mobile phones—the mobile phone group—and another group that will not receive the app reminder—the no mobile phone group. Group allocation will depend on whether the participant has a mobile phone and if its characteristics are adapted to the requirements of the study.

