### Educational Intervention

The therapist will go to each participant's home and perform an ergonomic assessment of the home. The therapist will also assess the execution of ADL by the participant using the home therapeutic advice for people who suffer stroke (HTAS) tool, which is a checklist of 60 items—the therapist will mark those items he valued as deficient. Later, with the experimental group, the therapist will mark on the participant’s advice sheet those items that were rated negatively and will advise them on how to solve these shortcomings. With this advice, the therapist will educate participants on the correct or easiest way to perform their daily tasks, on which adaptations they should make at home, and on what kind of technical assistance could be useful for them. Previous studies on the impact of stroke in patients have demonstrated that cognitive, communication, and physical weakness combined with environmental changes frequently cause changes in roles, routines, and daily occupations [8-11].

In stage 2 of the study, the app will be installed on the mobile phones of participants in the mobile phone group, which will remind them of the advice previously offered by the therapist. The timing of reminders will differ for each participant depending on the amount of advice they received. However, in the 18 weeks of the app being used, each piece of advice will be given as a reminder three times. The mobile phone will beep once for each piece of advice and the participant must check and mark the option indicating whether he has complied with the advice or not. Participants who will take part in the app intervention will have to answer at least 80% of the messages.

The app used in the study is called isoTimer (see Figure 1) and will be installed on participants’ phones who have a mobile phone with Android OS 3.2 or higher. For correct use of the app, the Google Calendar app will also be installed through which educational advice will be implemented and synchronized on the day and time scheduled by the researcher.

Because of the complications that can occur in this population with the use of mobile phones, the app has been designed to open and start working automatically when the mobile phone is switched on. At no time does the participant have to open the app.

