### Procedure

#### Overview

This goal of this study is to implement an educational intervention at home for patients who have suffered a stroke, in order to optimize or improve their performance of ADL after discharge from the hospital to their homes. This intervention will be divided into two stages. In stage 1, assessments will be carried out for the experimental group and the control group, but educational advice will only be provided to the former. Stage 2 comprises a pilot program in which a reminder app will be installed on the mobile phones of some of the participants of the experimental group in order to increase treatment adherence.

#### Stage 1

Stage 1 will begin with the collection of the participants’ demographic data through a questionnaire and by conducting various tests to measure primary and secondary outcome variables. Subsequently, the ergonomics of the home and the implementation of ADL from both the experimental group and the control group will be assessed using the HTAS tool, which was developed by the authors. For the development of the tool, a literature review was performed using the PubMed electronic database and by reviewing different practice guides about stroke. Subsequently, the HTAS tool was evaluated by a panel of experts composed of occupational therapists, physiotherapists, nurses, caregivers, and patients.

Following the assessment of each participant’s home and his or her performance of ADL, the therapist will provide the participants of the experimental group with a list of pieces of advice related to the HTAS tool items that were evaluated negatively. The advice will be aimed at changing the environment in which the participants execute the ADL. This may include facilitation in the execution of the ADL, promoting the active use of the affected side of the body in such execution, or to show them the most appropriate way of performing certain tasks according to their situation after the stroke.

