The evaluation of the variables and the execution of the advised tasks will be carried out at participants’ homes 2 and 4 weeks following the initial assessment. Researchers will analyze and compare the data obtained from the outcome variables of the experimental group and the control group to check whether the educational intervention was effective in patients who have suffered stroke and who have been discharged to their homes. If the hypothesis is confirmed, the educational intervention would be implemented in the control group.

#### Stage 2

For the pilot study in stage 2, one group will receive the app reminders on their mobile phones—mobile phone group—and another group will not—no mobile phone group. Placement in the first group depends on whether the participant has a mobile phone and if its characteristics are adapted to the requirements of the study. The app will provide the advice previously given by the therapist in the participants’ homes. The timing of reminders will differ for each participant depending on the amount of advice given. However, in the 4 weeks of the app being used, each piece of advice will be given three times. The mobile phone will beep once for each piece of advice and the participant must check and mark the option indicating whether he has or has not complied with the advice. After this period, the outcome variables will be analyzed in both groups to check whether there are differences between the two groups.

After 8 weeks, and after having removed the app from mobile phones of the mobile phone group, we will reanalyze the outcome variables. Will do this by testing both groups to see whether the mobile phone group participants have continued to perform the advised tasks provided by the therapist, and if differences still exist between them and the no mobile phone group. If so, a reminder system will be implemented in the no mobile phone group. Figure 2 shows the outline of the entire study protocol, including steps in stage 1 and stage 2.

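### Stage 2 forms its app and no-app groups by ownership of a compatible phone, so their difference mixes the app's effect with differences between owners and non-owners

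*Protocol article*

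**What the plan says.** In the protocol article, Randomization gives two different rules. For stage 1, two groups of 40 are randomized: "The assignment of subjects to each group will be made through a system of sealed envelopes". For stage 2 the rule is: "Group allocation will depend on whether the participant has a mobile phone and if its characteristics are adapted to the requirements of the study". Procedure, Stage 2 repeats it: "Placement in the first group depends on whether the participant has a mobile phone". Educational Intervention makes compatibility concrete: the app goes to participants "who have a mobile phone with Android OS 3.2 or higher".

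Procedure, Overview says that "a reminder app will be installed on the mobile phones of some of the participants of the experimental group" and labels the stage: "Stage 2 comprises a pilot program". Neither the number entering stage 2 nor the split between its groups is given.

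Statistical Analyses names one inferential model, a 2x2 mixed ANOVA. Its between-subjects factor is mobile phone group or no mobile phone group, its within-subjects factor is time (before and after), and the significance threshold is P<.05. No covariates are named. Pre-intervention values are to be compared.

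Procedure, Stage 2 also attaches an action to the later comparison, made 8 weeks on with the app removed. It asks whether the groups still differ and continues: "If so, a reminder system will be implemented in the no mobile phone group".

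**The concern.** Under this rule, receiving the app and owning a compatible phone are the same variable. No section randomizes among owners, supplies phones or matches the groups. The comparison therefore contains nobody with a compatible phone and no app, and nobody with the app who lacked such a phone.

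It is plausible, though the article does not quantify it, that phone ownership after stroke goes with age, cognition, hand function, resources and family support, and that these bear on recovery in daily activities and on adherence. Educational Intervention itself notes that phone use can be difficult in this population.

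At stake is the article's only evidence on its secondary aim, whether phone reminders help patients keep up the advice. The decision to extend reminders to the comparator group rests on the same contrast.

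**Working it through.** **Step 1. Does the stated analysis separate the two effects?** Write the expected change from before to after as

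- owners (app): m + a + b
- non-owners (no app): m

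Here m is the change common to all, a is the app's effect, and b is the difference in change that owners would have shown without the app. The group-by-time term of the 2x2 mixed ANOVA compares these changes:

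(m + a + b) − m = a + b.

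A difference between owners and non-owners that is constant over time is present before and after and cancels. A difference in the rate of recovery or in adherence is b and stays. Comparing pre-intervention values can reveal an imbalance, but it does not change a + b. The bias is b at any sample size.

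**Step 2. How large could the consequence be?** The article gives no stage 2 sample size or power to reproduce; its Sample Size Calculation covers stage 1 only. The following is an illustration, and every input except the threshold is an assumption:

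- 40 participants enter, all from the experimental group (its full size under Randomization);
- splits of 20 v 20, 15 v 25 or 10 v 30;
- a = 0;
- b = 0.2, 0.3, 0.5 or 0.8 SD of the change;
- two-sided test at .05. The threshold is from Statistical Analyses; two-sidedness is assumed.

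With two groups and two time points, the group-by-time test is equivalent to a two-sample t-test on change, with df = n1 + n2 − 2 = 38 and critical value 2.024. The noncentrality is

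δ = b × √(n1·n2/(n1+n2)).

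For 20 v 20 and b = 0.3: δ = 0.3 × √(400/40) = 0.3 × 3.162 = 0.949, and P(|t| > 2.024) = 0.152.

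For 10 v 30 and b = 0.3: δ = 0.3 × √(300/40) = 0.3 × 2.739 = 0.822, and P(|t| > 2.024) = 0.126.

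Chance of P<.05 when the app has no effect:

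| Split | b = 0.2 | b = 0.3 | b = 0.5 | b = 0.8 |
|---|---|---|---|---|
| 20 v 20 | 9.5% | 15.2% | 33.8% | 69.3% |
| 15 v 25 | 9.2% | 14.6% | 32.0% | 66.5% |
| 10 v 30 | 8.3% | 12.6% | 26.6% | 57.0% |

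The nominal rate is 5%.

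**Step 3. What would randomizing owners leave?** If half of 40 own a compatible phone (assumed), the comparison is 10 v 10, with df = 18 and critical value 2.101. At d = 0.8, δ = 0.8 × √(100/20) = 1.789 and power is 39.5%. At d = 0.5, δ = 1.118 and power is 18.5%.

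**The case against.** The best defence is one of proportion. Stage 2 is openly called a pilot, it serves a secondary aim, and its allocation rule is disclosed directly after the stage 1 method. The stage 1 comparison is randomized and untouched. All of this stands, and it limits the severity. It is also fair that covariates are often left to an analysis plan that is not shown. Their absence here is therefore not a fault in itself, but adjustment in at most about 40 people would reduce the confounding only in part.

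The illustration has no source in the article for the SD gaps, the total or the splits, and smaller gaps or more unequal splits give lower rates. It also models a continuous change score rather than adherence as such. It shows the mechanism and a range; it does not estimate the actual bias.

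Three stronger readings are tempting, and the text does not support them:

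- **That the follow-on rule contradicts the allocation, because people without a usable phone cannot receive the app.** The rule promises a reminder system, not the app. Another medium or supplied phones would satisfy it. What can be said is that the form is not stated, and that it may not be the app that was tested.
- **That the rollout is triggered by a P value.** Procedure, Stage 2 asks only whether differences still exist. The .05 threshold stands elsewhere, as a general rule.
- **That calling the study an RCT misdescribes it.** The label is correct for stage 1, and the article does not say that stage 2 is randomized.

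**Conclusion.** The point holds as a should-fix. Stage 2 allocation by ownership of a compatible phone makes the between-group contrast estimate a + b, and nothing in the stated analysis isolates a. Under the assumptions shown (40 entering, no app effect, gaps of 0.3 to 0.5 SD in change), a significant difference would appear in about 13% to 34% of such trials across splits from 10 v 30 to 20 v 20. The true gap is unknown, could be near zero, and could run in either direction.

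The contrast cannot by itself support a conclusion that the app improves adherence or function, nor a decision to extend reminders on that ground. The conclusion is confined to stage 2.

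**What to change.** **Preferred.** For participants of the experimental group who have not yet entered stage 2, identify those with a compatible phone and randomize them to app or no app with the sealed-envelope system already in use. Follow those without a compatible phone descriptively, outside the comparison. The analysis can keep its form, with randomized app or no app as the between-subjects factor.

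**If too few have phones, or stage 2 is already under way.** Describe stage 2 as a non-randomized exploratory pilot. Report estimates with confidence intervals adjusted for age, MMSE and end-of-stage-1 values, draw no efficacy conclusion, and do not make the extension of reminders depend on the between-group difference.

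In either case, state what the reminder system for the no mobile phone group would be.

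**Cost.** A short amendment and a second set of envelopes. The article reports that recruitment and intervention have begun, so this is a change during the trial. The comparison also becomes smaller: with 10 v 10, power is about 40% at d = 0.8 and 19% at d = 0.5. That is tolerable in a pilot with no stated power, provided it is reported as estimation. The fallback costs only wording, but it leaves residual confounding that adjustment cannot remove.
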